### 2.4. Sample size

Since PBC, the study’s target disease, is a rare disease, the total number of participants in the study’s participating facility is expected to be around 110, and it is estimated to be 100 after the dropout. The difference between the treatment groups (standard and high dose administration groups) from the start (0 weeks) to the end of administration (24 weeks) is 5%, and the standard deviation is 5%. With a 7.5% probability, a power of 90% can be obtained at a significance level (both sides) of 5%.

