#### 2.5.7. Data monitoring.

Serum levels of GGT, alkaline phosphatase, transaminase, and total bilirubin will be measured in the clinical laboratories in each facility. Those of tumor necrosis factor-alpha, interleukin 6, IL-1β, peroxisome proliferator-activated receptor-γ, superoxide dismutase, glutathione peroxidase, Nrf2, and HMOX-1 will be measured by the authors using the commercially available enzyme-linked immunosorbent assay kit. All data will be stored in a database in a locked cabinet at the laboratory of the Department of Gastroenterology and Hepatology at Nara Medical University. The assessors will enter the data into the database system. The trial enrollment and duration will be limited to ensure data robustness.

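### The stated 90% power does not follow from the stated SD of 5%; it is approximately reproduced only if the unexplained 7.5% is the SD

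*Protocol article*

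**What the plan says.** Section 2.4 of the protocol article starts from availability. Primary biliary cholangitis is rare, so the number of participants "is expected to be around 110, and it is estimated to be 100 after the dropout". Figure 1 gives 55 patients per group at enrolment. The planning difference between the two dose groups "from the start (0 weeks) to the end of administration (24 weeks) is 5"%. The SD and the power sentence follow: "the standard deviation is 5%. With a 7.5% probability, a power of 90% can be obtained at a significance level (both sides) of 5"%.

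Section 2.5.2 (Primary endpoint) names the test as an unpaired Student's t test on the mean relative change in GGT from week 0 to week 24. No other section mentions or explains the 7.5%.

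**The concern.** A power statement needs a difference, an SD, a sample size and a significance level, and section 2.4 gives a labelled value for each. The stated power should follow from them, and it does not. The sentence also contains a fifth figure, 7.5%, labelled as a probability, which has no place in a two-sample power calculation with a 5% significance level and 90% power.

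The two percentages lead to different views of the trial. On an SD of 5 points, 100 evaluable patients are more than twice what 90% power requires. On an SD of 7.5 points, the same 100 patients reach 90% with almost nothing to spare. The article does not say which view the planners held, so a reader judging how much variability the trial can absorb has no firm figure to use.

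**Working it through.** **Inputs, all from the protocol article**

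- Difference Δ = 5 percentage points in the relative change in GGT (2.4). Reading the 5% as percentage points fits the endpoint definition in 2.5.2.
- SD σ = 5 points as labelled (2.4); the alternative is 7.5 points.
- Evaluable patients: 100 of 110, a loss of 10/110 = 9.1% (2.4). Figure 1 has equal groups, so n = 50 per group.
- Two-sided α = 5%, stated power 90% (2.4).
- Unpaired Student's t test (2.5.2).

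**Formulas**

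Normal approximation: power = Φ[(Δ/σ)·√(n/2) − 1.960], and n per group for 90% power = 2·(1.960 + 1.282)²·(σ/Δ)². Each result was also obtained from the noncentral t distribution, which matches the planned test.

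**Step 1: the plan's labelled inputs (σ = 5)**

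- Δ/σ = 1.0 and √(50/2) = 5, so power = Φ(5.000 − 1.960) = Φ(3.040) = 99.88%. The t calculation gives 99.86%.
- n for 90% = 2 × 10.51 × 1.00 = 21.0, so 22 per group. The t calculation gives 22.02, so 23 per group, or 46 in total.

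The stated 90% is not reproduced.

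**Step 2: 7.5% read as the SD (σ = 7.5)**

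- Δ/σ = 0.667, so power = Φ(3.333 − 1.960) = Φ(1.373) = 91.5%. The t calculation gives 91.0%.
- n for 90% = 21.01 × 2.25 = 47.3, so 48 per group. The t calculation gives 48.3, so 49 per group, or 98 in total, against 100 planned.

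The stated 90% is approximately reproduced.

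**Step 3: other readings**

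| Reading | Power |
|---|---|
| σ = 5, 55 per group | 99.9% |
| 7.5% is the difference, σ = 5, 50 per group | over 99.9% |
| 7.5% is the significance level, Δ = 5, σ = 5, 50 per group | 99.9% |
| σ = 7.5, 50 per group, one-sided 5% | 95.2% (t) |
| σ = 7.5, 55 per group, two-sided 5% | 93.4% (t) |

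Of the readings tried, the one in step 2 comes closest to 90%. It is also the one that uses the plan's own evaluable number and its two-sided 5%.

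**Step 4: how much room the 90% leaves**

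At 50 per group and two-sided 5%, the t test has 90% power for a standardised difference of 0.655. A difference of 5 points therefore has 90% power up to σ = 5/0.6548 = 7.64 points. Equivalently, the detectable difference at 90% power is 0.655 × SD: 3.3 points at an SD of 5, and 4.9 points at an SD of 7.5.

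**The case against.** The strongest defence is that only the wording is faulty. The paragraph itself contains the figure that makes the numbers agree: put 7.5% in place of the SD and the difference, the significance level, the 100 evaluable patients and the 90% fit together. The planners may have considered an SD between 5% and 7.5% and quoted the power for the larger value, with the sense lost in translation or editing. Moreover, the number of patients was set by how many the centres can recruit, and power was stated afterwards. Nothing in the design or analysis depends on the sentence. The primary analysis also commits to a point estimate and 95% confidence interval, which will show what a null result excludes whatever SD was assumed.

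Most of this stands, and it limits the point to the sentence itself. It does not clear the sentence. To reach the consistent reading, one must set aside the only figure labelled as an SD and replace the word *probability* with another term.

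One could also take "a power of 90% can be obtained" as a floor, since 99.9% exceeds 90%. That leaves the 7.5% with no function and still hides the power that the labelled inputs give.

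A reader might go further and infer that the sample-size plan is wrong, or that the trial is underpowered because GGT must vary more than either figure allows. The documents do not support this. They give no data on the variability of GGT change, so neither SD can be called implausible from them. The local measurement of GGT ("will be measured in the clinical laboratories in each facility") does not settle it either: the endpoint is each patient's change relative to their own baseline, and a constant proportional difference between laboratories cancels if both samples go to the same one. The lack of a cited source for the SD is no fault in a journal article that condenses a fuller protocol.

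**Conclusion.** The power statement in section 2.4 is wrong as written. Its labelled inputs give 99.9% power, against the 90% claimed, and would need 23 patients per group for 90%, against 50 planned. The *7.5% probability* has no meaning in its place.

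The sample size itself is not shown to be wrong. If the 7.5% is the SD, power is 91.0%, and the plan holds together with a margin of 1 patient per group (49 needed, 50 planned). That is the most plausible reading, but it remains an inference until the sponsor confirms it. Under it, the 90% holds for SDs up to about 7.6 points.

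The figures assume 50 evaluable patients per group, a common SD, the difference and SD both in percentage points of relative change, and the unpaired t test of section 2.5.2.

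**What to change.** Correct the sentence in section 2.4 so that it says what the 7.5% is and which SD the 90% power rests on. If the sponsor confirms that 7.5% is the SD, wording such as this would do:

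> Fifty evaluable patients per group give about 91% power (two-sided 5%) to detect a difference of 5 percentage points if the SD is 7.5 points, and 99.9% if the SD is 5 points.

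If the 7.5% means something else, say what it is and recompute the power from the SD actually assumed. Optionally, add that the detectable difference at 90% power with 50 per group is 0.655 × SD, so that readers can apply their own value.

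The cost is one sentence. The number of patients, the endpoint and the test do not change. The only downside is that the stated power becomes openly conditional on the SD.

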### 2.5. Statistical analysis

#### 2.5.1. Collection of background (baseline) data.

The background (baseline) data of the research subjects will be tabulated. For nominal and ordinal variables, the frequency and proportion of categories will be calculated. For continuous variables, summary statistics such as mean, standard deviation, minimum, median, and maximum will be calculated. Values of *P* < .05 will be considered as statistical significance. JMP version 14.3 (SAS Institute Inc, Cary, NC) software and EZR software, which is a GUI for the R statistical computing and graphics environment,^[23]^ will be used for statistical analyses.

#### 2.5.2. Primary endpoint.

The average “rate of change of biliary enzyme levels (serum GGT levels) at 24 weeks after glucosyl hesperidin administration from before administration (0 weeks)” will be compared between groups using an unpaired Student’s *t* test. In addition, the point estimate of the difference between the groups and the 95% confidence interval will be calculated.

The rate of change will be calculated as follows: serum GGT level (24 weeks)-serum GGT level (0 weeks)/serum GGT level (0 weeks).

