### 2.2. Randomization

The study participants will be registered and allocated using stratified permuted block randomization. Participants will be randomly assigned to either the 500 mg/day or 1000 mg/day groups based on the following factors: registered facility and patient sex. Table 2 provides an overview of all visit and test schedules.

**Table 2 T2:** An overview of observation, clinical examination, and evaluation.

	Screening within 1 month	Obtaining informed consent within 1 month	Observation period					
			Treatment start date	8 weeks	16 weeks	24 weeks	36 weeks	At the time of discontinuation
Permissible range (weeks)				±2	±2	±2	±4	
Visits		1^st^	2^nd^	3rd	4th	5th	6th	
Allocation		✓						
Patient’s characteristics	✓	✓						
Treatment								
Adherence check			✓	✓	✓	✓		
Subjective symptoms	✓	✓	✓	✓	✓	✓	✓	✓
Adverse events			✓	✓	✓	✓	✓	✓
Blood examination			✓^*1^	✓	✓	✓	✓	✓^*2^

✓ means the day for each event in left column. *1: This examination can be omitted if a blood test is performed during the screening period or consent is obtained. *2: This examination can be omitted if patient consent cannot be obtained.

AEs = adverse events.

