#### 2.5.3. Secondary endpoint.

For each item, the mean values for each group will be compared between groups using an unpaired Student’s *t* test. In addition, the point estimate of the difference between the groups and the 95% confidence interval will be calculated. The rate of change will be calculated as follows: each evaluation item (at each evaluation point other than 0 weeks) – each evaluation item (0 weeks)/each evaluation item (0 weeks). The following items will be included: Rate of change in biliary enzyme levels (serum GGT level) after glucosyl hesperidin administration (8 and 16 weeks) from before administration (0 weeks); rate of change in hepatobiliary enzyme levels (serum alkaline phosphatase, transaminase, and total bilirubin levels) after glucosyl hesperidin administration (8, 16, and 24 weeks) from before administration (0 weeks); and rate of change in Nrf2 protein expression levels and its target gene (HMOX-1) after glucosyl hesperidin administration (8, 16, and 24 weeks) from before administration (0 weeks).

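### The primary t test leaves out the stratification factors and baseline GGT; adjusting is cheap, but the gain cannot be computed from the article and baseline adjustment adds almost nothing at the planning SD

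*Protocol article*

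**What the plan says.** Section 2.2 states that participants are "registered and allocated using stratified permuted block randomization", with assignment "based on the following factors: registered facility and patient sex".

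Section 2.5.2 fixes the primary analysis. The mean rate of change in GGT from week 0 to week 24 "will be compared between groups using an unpaired" Student's t test, and "the point estimate of the difference between the groups and the 95% confidence interval will be calculated". The outcome is printed as "serum GGT level (24 weeks)-serum GGT level (0 weeks)/serum GGT level (0 weeks"), which I read as the week-24 minus week-0 difference divided by the week-0 value. No covariate, transformation or stratified analysis is named.

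Sections 2.5.3 and 2.5.4 use the same test for the secondary and exploratory markers; section 2.5.3 says "the mean values for each group will be compared between groups using an unpaired" t test.

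Section 2.4 plans on a between-group difference in change "from the start (0 weeks) to the end of administration (24 weeks) is 5"%, prints an SD of 5%, and expects about 110 participants, 100 after dropout. It adds: "With a 7.5% probability, a power of 90% can be obtained at a significance level (both sides) of 5"%.

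**The concern.** Two features of the analysis do not use what the design provides.

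- **Stratification.** Stratified blocks balance facility and sex between the arms. When those factors predict the outcome, this removes their contribution from the true variance of the treatment difference. The unpaired t test still counts that contribution in its standard error, so the test runs below its nominal 5% level and the interval is too wide. A facility effect is plausible, because section 2.5.7 has GGT measured in each facility's own laboratory.
- **Scale and baseline.** Percentage change cannot fall below -100% but has no upper limit, so it tends to be right-skewed. Table 1 sets no GGT range for entry. Baseline enters only as the denominator, so a chance imbalance between arms is not otherwise corrected.

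At stake is precision in a trial whose size is limited by the rarity of the disease (section 2.4). Baseline GGT, facility and sex are already recorded.

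**Working it through.** **1. The plan's own figure.** Inputs from section 2.4 and Figure 1: difference 5, two-sided alpha 0.05, 50 evaluable per arm. Standard error = SD × √(2/50); power ≈ Φ(5/SE − 1.96).

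- SD 5, as printed: SE = 1.0; Φ(5.00 − 1.96) = 99.9%. This does not reproduce 90%.
- SD 7.5: SE = 1.5; Φ(3.333 − 1.96) = 91.5% (91.0% with the noncentral t). This does.

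The stated power therefore fits only if 7.5% is the SD. I use 7.5 below as an assumption.

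**2. Leaving out the stratification factors.** Let R² be the share of outcome variance that the factors explain. R² is not in the article; 0 to 0.3 is assumed. With the factors fully balanced, the true SE is 1.5 × √(1 − R²), while the t test still uses about 1.5. Then:

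- SE overstated by 1/√(1 − R²)
- t test's type I error = 2 × [1 − Φ(1.96/√(1 − R²))]
- t test's power = Φ((3.333 − 1.96)/√(1 − R²))
- adjusted power = Φ(3.333/√(1 − R²) − 1.96)

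| R² | SE too large by | Type I error, t test | Power, t test | Power, adjusted |
|---|---|---|---|---|
| 0 | 0% | 5.0% | 91.5% | 91.5% |
| 0.1 | 5.4% | 3.9% | 92.6% | 94.0% |
| 0.2 | 11.8% | 2.8% | 93.8% | 96.1% |
| 0.3 | 19.5% | 1.9% | 95.0% | 97.9% |

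A simulation with the facility effect varied agrees (100 patients, blocks of 4, difference 5, SD 7.5; assumed 5 sites and 15% men; 5,000 runs):

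| Variance explained by facility | Type I error, t test | Power, t test | Power, adjusted | Gain (points) |
|---|---|---|---|---|
| 0% | 4.7% | 91.0% | 90.6% | −0.4 |
| 10% | 3.8% | 90.9% | 92.3% | 1.4 |
| 20% | 2.8% | 92.8% | 95.3% | 2.5 |
| 30% | 2.5% | 94.1% | 97.7% | 3.6 |

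**3. Baseline adjustment at the planning SD.** With equal variances at both visits, ANCOVA's residual variance relative to the log-change score is (1 + ρ)/2, where ρ = 1 − SD²/(2s²) and s is the between-patient SD of log GGT. The article does not give s; 0.4 to 1.0 is assumed.

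- s = 0.4: ρ = 1 − 0.005625/0.32 = 0.982; variance saved (1 − ρ)/2 = 0.9%.
- s = 1.0: ρ = 1 − 0.005625/2 = 0.997; variance saved 0.1%.

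Simulated power at s = 0.5 and 0.8 (10,000 runs each) is 92.4% and 92.6% for the t test on percentage change, against 92.5% and 92.4% for log-scale ANCOVA. There is no difference beyond simulation error.

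**4. If GGT change varies much more than planned.** Same simulation. The effects had to be raised above the planned 5% to keep power in a readable range, so both columns of inputs are assumptions.

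| SD of log change | Assumed reduction | s | t test | Log ANCOVA | Gain (points) |
|---|---|---|---|---|---|
| 0.2 | 12% | 0.5 | 88.7% | 89.7% | 1.0 |
| 0.2 | 12% | 0.8 | 88.2% | 89.1% | 0.9 |
| 0.3 | 18% | 0.5 | 89.4% | 92.9% | 3.5 |
| 0.3 | 18% | 0.8 | 89.8% | 91.7% | 1.9 |
| 0.4 | 22% | 0.5 | 84.1% | 91.6% | 7.5 |
| 0.4 | 22% | 0.8 | 83.9% | 88.2% | 4.3 |
| 0.5 | 27% | 0.5 | 83.2% | 94.6% | 11.4 |
| 0.5 | 27% | 0.8 | 83.0% | 90.4% | 7.4 |

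With no treatment effect and no stratum effects, the t test on percentage change rejected in 4.7% to 5.3% of runs.

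**The case against.** The strongest reply is that nothing here is contradictory. Endpoint (section 2.3), sample size (section 2.4) and analysis (section 2.5.2) all concern a mean rate of change, and omitting stratification factors errs on the safe side. That stands: a reader might infer that the t test is invalid or inflates false positives, and the checks show neither.

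A reader might also infer that log-scale ANCOVA is clearly more precise in this trial. At the trial's own planning figures it is not (step 3). The gains in step 4 need both a larger SD and a larger effect. With percentage-change SDs of about 24%, 63% and 88% and the planned 5% effect, simulated power is 19% against 19%, 6.5% against 7.5%, and 6.6% against 6.7% (t test against log ANCOVA), so neither method would rescue the trial.

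Three further limits hold:

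- Baseline GGT is not ignored, since it is the denominator; it is only not adjusted for.
- It is tempting to say that near-zero ELISA baselines would make the secondary and exploratory ratios unstable, but the article gives no assay values or detection limits to support that.
- Many small facilities would cost degrees of freedom, and the article does not give their number.

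An unseen analysis plan may add adjusted sensitivity analyses. That does not settle the point, because the article names the unadjusted t test as the primary analysis.

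**Conclusion.** The point holds as one of efficiency and consistency with the design, not of validity. The primary analysis omits both factors used in allocation. If they predict GGT change, the test is conservative and the interval too wide. The cost is about 0 to 4 power points for an assumed 0% to 30% of variance explained, taking an SD of 7.5% and, in the simulation, 5 sites. The true figure cannot be derived from the article.

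The case for baseline adjustment and the log scale is protection against skewness and chance imbalance. Its power gain is nil at the planning SD and about 1 to 11 points at assumed log-change SDs of 0.2 to 0.5 with effects of 12% to 27%. When facility explains nothing, adjustment costs under half a point of power. The change is worth making, but the trial does not fail without it.

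**What to change.** Before data lock, make the primary analysis a linear model with treatment, baseline GGT, sex and facility, with small facilities pooled by a rule written down in advance. Preferably model log GGT at week 24 with log baseline GGT as covariate, and report the 1000 mg to 500 mg ratio of geometric means with its 95% confidence interval, expressed as a percentage difference. Keep the t test on percentage change as a sensitivity analysis.

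The model needs no new data and can be fitted in the software named in section 2.5.1. The costs are a few degrees of freedom and, on the log scale, a changed estimand: the endpoint wording in section 2.3 and the 5% planning difference and SD in section 2.4 must be restated as a ratio. If the sponsor wants to keep the percentage-change endpoint, adding the same covariates to a linear model on that scale still brings the analysis into line with the randomisation.

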#### 2.5.3. Secondary endpoint.

For each item, the mean values for each group will be compared between groups using an unpaired Student’s *t* test. In addition, the point estimate of the difference between the groups and the 95% confidence interval will be calculated. The rate of change will be calculated as follows: each evaluation item (at each evaluation point other than 0 weeks) – each evaluation item (0 weeks)/each evaluation item (0 weeks). The following items will be included: Rate of change in biliary enzyme levels (serum GGT level) after glucosyl hesperidin administration (8 and 16 weeks) from before administration (0 weeks); rate of change in hepatobiliary enzyme levels (serum alkaline phosphatase, transaminase, and total bilirubin levels) after glucosyl hesperidin administration (8, 16, and 24 weeks) from before administration (0 weeks); and rate of change in Nrf2 protein expression levels and its target gene (HMOX-1) after glucosyl hesperidin administration (8, 16, and 24 weeks) from before administration (0 weeks).

#### 2.5.4. Exploratory endpoint.

For each item, the mean values for each group will be compared between groups using an unpaired Student’s *t* test. In addition, the point estimate of the difference between the groups and the 95% confidence interval will be calculated. The rate of change will be calculated as follows: each evaluation item (at each evaluation point other than 0 weeks)-each evaluation item (0 weeks)/each evaluation item (0 weeks).

The following items will be included: The rate of change in the protein expression level of inflammatory cytokines (tumor necrosis factor-alpha, interleukin 6, and IL-1β), as well as peroxisome proliferator-activated receptor-gamma (peroxisome proliferator-activated receptor-γ), superoxide dismutase, and glutathione peroxidase, which have an inhibitory effect on the activation of the inflammation/immune-related transcription factor nuclear factor-kappa B before and after glucosyl hesperidin administration (0–8, 0–16, and 0–24 weeks).

#### 2.5.5. Other analysis items.

The ratio for each research subject and the average will be calculated to determine adherence. In particular, the previous dose intake rate corresponds to: 70% or more, 30% or more and less than 70%, or less than 30% for each visit during the period of glucosyl hesperidin administration.

#### 2.5.6. Safety analysis.

All AEs will be evaluated according to the Common Terminology Criteria for Adverse Events version 5.0 proposed by National Cancer Institute. The incidence of each AE will be calculated in the glucosyl hesperidin-administered subjects during the study’s observation period. The period for collecting data related to all evaluation items will be completed for all analyses, and the analysis will be performed once the data is fixed.

#### 2.5.7. Data monitoring.

Serum levels of GGT, alkaline phosphatase, transaminase, and total bilirubin will be measured in the clinical laboratories in each facility. Those of tumor necrosis factor-alpha, interleukin 6, IL-1β, peroxisome proliferator-activated receptor-γ, superoxide dismutase, glutathione peroxidase, Nrf2, and HMOX-1 will be measured by the authors using the commercially available enzyme-linked immunosorbent assay kit. All data will be stored in a database in a locked cabinet at the laboratory of the Department of Gastroenterology and Hepatology at Nara Medical University. The assessors will enter the data into the database system. The trial enrollment and duration will be limited to ensure data robustness.

